#### Consent

A study information letter will be sent to all eligible families, followed by a phone call. Informed consent will be obtained from all eligible participants who express interest in participating, and if required, from substitute decision makers.

The study will be introduced to all prospective participants in an in-person meeting, where the study personnel will use her judgment to determine whether the youth would provide consent or assent. If a participant demonstrates a clear understanding and appreciation of the purpose of the study and his/her rights regarding participation, consent will be obtained directly. If the young person demonstrates a partial understanding, parental consent and participant assent will be obtained. If a participant does not have a reliable means of communicating yes/no, consent for study participation will be obtained from a substitute decision maker, such as a parent. Prospective youth consent will include acknowledgement of the quantitative assessments of secondary outcomes related to health, well-being, social participation, and transition readiness; permission for the research team to access their health care utilization data held within the administrative databases maintained by the Ministry of Health and Long-Term Care (MOHLTC) and individually identified primary pediatric and adult health care facilities, and participation in qualitative interviews regarding their transition experience.

All retrospective participants will receive the consent packages by mail if they express interest in participating during the initial phone call. Thus, the parent and youth will be responsible for making this decision jointly, and they will be sent all versions of the consent materials. Retrospective primary participant consent will include the release of health care numbers and permission to review pediatric and adult health service use through identified administrative database reviews and chart audits. All participants will be informed at the time of consent that they can withdraw from the study at any point in time. Data collection would cease as of the date of withdrawal and outstanding MOHLTC information release forms would be destroyed.

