### Measures

#### Quantitative data

The identification of specific measures for the study was influenced by the transition literature
[13,14]; however, the availability of outcome measures straddling the significant developmental periods arising between infancy and adolescence with consideration of varied cognitive impairments and normative trajectories has long posed a challenge in pediatric rehabilitation
[40]. Beyond measures of quantity and quality of care (e.g., satisfaction with service delivery, medical record documentation) and continuity of care (e.g., attendance rates, patient satisfaction, treatment adherence, etc.), there are no universally identified outcomes that define a ‘successful’ transition
[8,30,34,41,42], as the complexity of interaction of contributing factors is not well understood
[8,43]. In this study, the International Classification of Functioning, Disability and Health (ICF) will be used to ensure a broad focus on body function and structure, activity, and participation
[44]. The LETS study will examine several groups of outcomes of the transition process as facilitated by the LIFEspan model. Thus, we will use a combination of measures that assess skills that have been identified in the literature through descriptive research as central to successful transition (although yet not empirically proven). In doing so, the choice of study measures reflects a multidimensional approach to transition. The outcomes of the LETS study and corresponding measures for data collection related to each outcome are summarized in Table 
1. 

**Table 1 T1:** Outcomes and Measures

**Outcomes**			**Contributors**	**Quantitative Data Sources**		
				**MOHLTC**	**Chart**	**Self-Report**
**Primary**	Pediatric & Adult Medical Specialists		All	☑	☑	
	Family Doctor		All	☑		
	Pediatric Allied Specialists		All		☑	
	Adult Allied Specialists		Prospective			☑ Allied Care Form (LETS Study-Specific Questionnaire)
**Secondary**	Emergency Care & Hospitalizations		All	☑		
	Transition Readiness		Prospective			☑ *Self-Management:* Partners in Health Scale [45]
						☑ *Self-Determination:* Arc’s Self-Determination Scale [46]
						☑ *Self-Efficacy:* Self-Efficacy for Managing Chronic Disease [47]
	Participation		Prospective			☑ *Participation:* Community Involvement Form (LETS Study-Specific Questionnaire)
						☑ *Life Habits:* “Assessment of Life-Habits” [48]
						☑ *Social Support:* Multidimensional Scale of Perceived Social Support [49]

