	Health & Well-Being		Prospective			☑ *Health Status:* Self-Rated Health Scale [50]
						☑ *Quality of Life*: Assessment of Health-related Quality of Life [51], Health Utilities Index [52]
**Demographics**			All		☑	☑ Demographic Information Form (LETS Study-Specific Questionnaire

For the primary outcome of interest related to the LIFEspan model of linked health care, we will capture continuity of care between the ages of 18 (discharge from the pediatric centre) and 19 years (one year post-discharge). Continuity of care is not an all-or-nothing outcome
[44]; therefore, a study-specific scale will be used to classify participants as having continuity of care on several levels (i.e., achieving a formal discharge from a pediatric facility; having a referral or seeing at least one medical specialist analogous to currently seen pediatric professional; having access to a family physician, etc.). The continuity of care score will be assigned to each participant in their final year of this longitudinal study based on reviewing their health care utilization data, which will include primary care as reflected by MOHLTC summaries, and transition care as abstracted from participant charts (Table 
1).

Secondary outcome measures will include patterns of hospitalizations and emergency care utilization, and measures of health and well-being, participation, and transition readiness. As summarized in Table 
1, patterns of hospitalizations and emergency care will be determined from MOHLTC summaries that provide information on frequency and duration of access, which we expect will vary as a function of continuity of care. All other outcomes will be obtained through personal assessments using standardized and study-specific tools. A demographic questionnaire and community participation form were developed specifically for the study. Three different standardized measures of health and well-being will be used: the self-rated health scale from the National Health Interview Survey
[50], the Health Utilities Index (HUI3
[52]), and the Assessment of Health-related Quality of Life (AQoL
[51]). Young et al.’s work provides health status scores for the HUI3 and the health scale for youth and adults with CP, ABI, and SB
[13]. These historical data will be valuable in understanding the patterns of change in the current study. The LIFE-H

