### Data collection

#### Study timeline

The inclusion of three different disability groups raises the possibility of differences arising as a function of disability-related influences rather than the transition intervention. To offset this possibility, baseline measures will be sampled twice to document existing differences within the three prospective participant groups and reduce individual variability, resulting in three different data collection periods for ABI and CP groups (Table 
2). The first baseline will occur at 17 years of age and correspond to the completion of year 1 of LIFEspan. The second will occur at 18 years of age, just prior to discharge, corresponding to the end of year 2 of LIFEspan. Follow-up measurement of outcomes of interest will occur at 19 years of age and correspond to 1 year post-transfer. Additionally, participants will be contacted bi-annually to complete specific survey materials (i.e., community involvement and allied health care surveys) to ensure a short window of recollection. SB group data will also be collected at these age markers, though this group will not have had exposure to LIFEspan. For retrospective participants, once consent is received, the ABI/CP participants will be ‘followed’ for a three-year period preceding introduction of the LIFEspan model. This window will match the age-related collection periods outlined for the prospective participants (i.e., first and second baseline, and post-transfer).

**Table 2 T2:** Timeline of the Study

**Protocol Events**	**Timeframe**		
	**Year 1**	**Year 2**	**Year 3**
	**Baseline 1**	**Baseline 2**	**Outcomes**
	**Age: 16-17**	**Age: 17-18**	**Age: 18-19**
	**1 Year Pre-Transition**	**Transition Year**	**1 Year Post-Transition**
***Recruitment and Consent***	☑		
***Demographic Questionnaire Form***	☑		
***MOHLTC Billing Summaries***	☑	☑	☑
▪ Medical Specialists			
▪ Family Doctor			
▪ Emergency Services & Hospitalizations			
***Chart Audit***	☑	☑	☑
▪ LIFEspan Service Delivery Description			
▪ Demographics, Functional Level, & Diagnoses			
▪ Medical Specialists			
▪ Hospital Allied Care			
***“Allied Care” and “Community Involvement” Forms***	☑	☑	☑
▪ Community Allied Care	+ 6-months follow-up	+ 6-months follow-up	+ 6-months follow-up
▪ Vocation, Recreation, Social Activities, & Sports			
***Self-Reported Secondary Measures***	☑	☑	☑
▪ Transition Readiness			
▪ Health Status & Well-Being			
▪ Participation			
***Youth and Parent Interviews***			☑

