Several limitations of this study should also be recognized. First, drop-out is always a significant risk in longitudinal designs. However, subject attrition for primary measures of continuity of care is expected to be minimal as permission for data release was sought at the outset of the study, and administrative database interrogation does not require continued participant contact. Unless a participant withdraws from the study, the primary outcome will be available on all participants, irrespective of loss to follow-up. In addition, key demographic data were also obtained at the time of consent; this information will allow for a detailed comparison of participants who completed the study with those that did not. However, subject attrition will still be concerning for secondary measures. Second, since this project is a longitudinal prospective cohort study of the LIFEspan model, the representativeness of the sample is also a potential risk. At present, the LIFEspan model is only available for clients of one pediatric centre. The centre is recognized as Canada’s largest rehabilitation centre and is located in a large multi-cultural urban area of Ontario. As such, LIFEspan does set the stage for an ideal model for which to strive in service delivery, where, for example, LIFEspan clients benefit from a publicly funded health care system and transportation services to and from the centre. However, generalizability of the LETS study is thereby somewhat limited, as these services and such multicultural populations might not be found in other jurisdictions. Third, the inclusion of three different disability groups also does raise the possibility of differences arising as a function of disability-related influences and not the intervention. While the standardized measures in this study have been selected based on their appropriateness for completion by people with disabilities, it is well recognized that individuals with physical and developmental disabilities may not follow the same developmental trajectory as their age-matched peers and as such, normative milestones may not be valid
[61].

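### Table 1 puts a prospective-only, self-reported adult allied care item in the primary outcome, contradicting the score's stated sources, the power definition and the claim that the outcome is available on everyone

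*Protocol article*

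**What the plan says.** In Table 1 (Measures, Quantitative data) the primary block has four rows. Medical specialists, family doctor and pediatric allied specialists are contributed by all participants, from Ministry data, charts or both. The fourth row, "Adult Allied Specialists", is contributed by the prospective groups only. Its single ticked source is self-report, on the study's Allied Care Form.

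The form depends on repeated contact. Under Study timeline, "participants will be contacted bi-annually to complete specific survey materials (i.e., community involvement and allied health care surveys" is the arrangement. Retrospective participants consent instead to "permission to review pediatric and adult health service use through identified administrative database reviews and chart audits".

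Three other places describe the primary outcome differently:

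- The text after Table 1 assigns the score from utilization data that include "primary care as reflected by MOHLTC summaries, and transition care as abstracted from participant charts". It cites Table 1 but does not name the form.
- Power calculation defines continuity as one or more primary care visits in the first year after transition.
- The Discussion states that, unless someone withdraws, "the primary outcome will be available on all participants, irrespective of loss to follow-up". Its reason is that "administrative database interrogation does not require continued participant contact".

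**The concern.** The Discussion's reasoning holds for database and chart components. It does not hold for an item that exists only if a participant fills in a form, and the retrospective cohort is never given that form. As Table 1 composes the primary outcome, the availability claim is false.

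The retrospective ABI/CP cohort is at stake. Under Participants it is added because spina bifida may confound the main comparison through different medical issues, and Data analyses plans a contrast of LIFEspan against it. If LIFEspan participants can gain credit from a source closed to that cohort, the contrast meant to deal with confounding carries a measurement difference of its own. Covariate adjustment cannot remove it, because the item is observed on one side only. Separately, loss to contact, which the Discussion treats as a worry for secondary measures, would also reach the primary outcome.

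**Working it through.** **1. The passages side by side**

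| Place | Adult allied care in the primary outcome? | Available in the retrospective cohort? | Survives loss to contact? |
|---|---|---|---|
| Table 1, primary block | Yes | No (prospective, self-report only) | No |
| Measures text on the score | Not named; list of levels left open | Yes, for the named sources | Yes |
| Power calculation | No (primary care visit) | Yes | Yes |
| Discussion | Implied no | Claimed yes | Claimed yes |

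The first row cannot be true together with the last.

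**2. How many participants**

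Planned sizes (Participants): LIFEspan 30 + 50 = 80; spina bifida 21; retrospective 15 + 20 = 35; total 136.

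- Without the form by design: 35/136 = 26%.
- Assume that 10%, 20% or 30% of the 80 + 21 = 101 prospective participants stop returning forms. Adding about 10, 20 or 30 gives about 45, 55 or 65 of 136, or 33%, 41% or 48%.

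**3. Illustrative size for the retrospective contrast**

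The plan has no figure for this item. Its one related figure, 90% power for 70 v 18 at 75% v 25%, comes out at 98.6% with the formula below (two-sided 0.05) and 97.6% by Fisher's exact test. That mismatch is a separate matter and nothing here depends on it.

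Assumptions: any one component counts as continuity; absent data count as not met; the true rate p on the shared components is the same in both groups; and a share q of LIFEspan participants otherwise without continuity report adult allied care. Then

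- LIFEspan rate = p + (1 − p)q; retrospective rate = p; spurious difference d = (1 − p)q.
- Probability of a significant result favouring LIFEspan = Φ[(d − 1.96 × SE pooled) / SE unpooled], with 80 v 35.

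Example with p = 0.25 and q = 0.20:

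- LIFEspan rate = 0.25 + 0.75 × 0.20 = 0.40, so d = 0.15.
- Pooled rate = (35 × 0.25 + 80 × 0.40)/115 = 0.354.
- SE pooled = √[0.354 × 0.646 × (1/35 + 1/80)] = 0.0969.
- SE unpooled = √[0.25 × 0.75/35 + 0.40 × 0.60/80] = 0.0914.
- (0.15 − 1.96 × 0.0969)/0.0914 = −0.44, so the probability is 33%.

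| p | q = 10% | q = 20% | q = 30% |
|---|---|---|---|
| 25% | 7.5 points, 12% | 15 points, 33% | 22.5 points, 63% |
| 50% | 5 points, 7% | 10 points, 17% | 15 points, 33% |
| 75% | 2.5 points, 5% | 5 points, 9% | 7.5 points, 16% |

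The formula counts only rejections in LIFEspan's favour, where the nominal rate is 2.5%. If the item is not scored, d = 0 and there is no inflation. If it were required for continuity and absence counted as failure, no retrospective participant could qualify.

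**4. The spina bifida contrast**

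Both prospective groups complete the same form, so there is no structural difference. Only attrition applies.

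**The case against.** A reader might infer that the retrospective comparison is biased towards LIFEspan. The documents do not establish that. The levels named in the Measures text are formal discharge, a medical specialist link and access to a family physician; allied care is not among them. The named sources are Ministry summaries and charts. The power definition needs only a primary care visit, which Ministry data give for every cohort. On either of these readings the built-in difference is zero. This objection stands, and it makes the bias conditional. It does not remove the contradiction: the list of levels is open-ended, the Measures text itself cites Table 1, and Table 1 marks the row as prospective-only yet keeps it under primary.

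A reader might also infer that adult allied care is wholly unobservable in the retrospective cohort. Table 2 does not support that. It lists hospital allied care under the chart audit in all three years and ties the form to community allied care, so hospital-based care may be recoverable from charts. Table 1 ticks no chart source for the adult allied row, so the two tables need reconciling.

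Larger error rates can be produced by treating the score as a count of the four Table 1 rows and applying a t-test. No such scoring is stated, and Data analyses plans logistic regression for continuity of care.

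On attrition, the Discussion excepts withdrawals, and the data collection section provides follow-up calls, mail-outs and proxy completion. These reduce missing forms but do not make the claim true for a form-based item. The missing scoring rule may sit in the full protocol and is not the complaint here.

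**Conclusion.** The contradiction holds on the article's own text: the availability statement is false for the primary outcome as Table 1 composes it, and Table 1 does not match the score's named sources or the power definition.

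The consequence depends on which passage governs. If the Table 1 item counts, the 35 retrospective participants cannot be credited from the form, the same-diagnosis contrast tilts towards LIFEspan, and lapsed prospective participants have missing primary data. If the Measures sources or the power definition govern, there is no bias and Table 1 is the error. The LIFEspan versus spina bifida contrast is exposed to attrition only.

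The size is illustrative. It starts at no inflation and reaches about 12% to 63% false positives at 80 v 35 under the any-component rule with a 25% common rate and 10% to 30% extra credit. It is lower at higher common rates. The scoring rule, the common rate and the allied care share are all assumptions; the article gives none of them for this item.

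**What to change.** Build the primary continuity outcome, at least for the retrospective contrast, only from Ministry and chart components abstracted in the same way in all cohorts. Move the Allied Care Form item to a secondary outcome for the prospective groups, and correct Table 1 to match. If hospital-based adult allied care from charts is meant to count, show the chart source in Table 1, in line with Table 2, and abstract it identically for every cohort. The Discussion's availability statement then holds, apart from withdrawals.

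If the form item stays in the primary score, limit that statement to the database and chart components.

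The cost is one item lost from the primary score, and with it self-reported community allied care. The form is still collected. At the plan's 75% v 25%, 80 v 35 has power above 99.9% without the item, so no planned power is given up.

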## Abbreviations

ABI: Acquired brain injury; CP: Cerebral palsy; LETS: Longitudinal Evaluation of Transition Services; LIFEspan: Living Independently and Fully Engaged Across the Lifespan; SB: Spina bifida; MOHLTC: Ministry of Health and Long-Term Care.
